### Objectives {7}

This study is designed to evaluate the efficacy and safety of EA for the prevention of negative moods after SD. Moreover, the effects of EA on mood after SD at different time points will be compared. The findings of this trial will provide more reliable evidence for clinical acupuncture prevention in the treatment of negative moods after SD.

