#### Blank control group

Participants in the blank control group will not be given any treatment.

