### Sample size {14}

This is an RCT study with three groups: an AE group, a NAE group, and a blank control group. The POMS will be the primary outcome measure observed. According to the findings of the clinical pre-trial study, the means of the POMS scores for each group are 8.26, 18.25, and 15.24, with standard deviations of 3.18, 5.96, and 5.42, respectively. The sample size was calculated by the PASS software (version 15.0.5, NCSS, LLC) [39], and at least 33 subjects will be needed in our study if the power is 0.9 and *α* is set to 0.05. To compensate for a 20% loss to follow-up, the sample size will be increased to 42 participants, of which at least 14 participants will be required in each group.

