## Statistical methods

### Statistical methods for primary and secondary outcomes {20a}

Descriptive statistics will be used to describe the study population. Comparisons of the study groups by age, gender, and outcome characteristics will be done using analysis of variance (ANOVA) or chi-square tests. Depending on whether the data are normally distributed, the continuous variables will be described as the mean (standard deviation) or the median. One-way analysis of variance (ANOVA) will be used for comparisons among the three groups. Continuous variables, including the POMS scores, PANAS scores, and FaceReader, will be compared among the three groups at all time points using ANOVA. The Student-Newman-Keuls method will be used for pairwise comparisons. Adverse events will be summarized for each group and compared using Fisher’s exact tests. Statistical analyses will be performed using SAS 9.1.3. Statistical significance will be set at *p* ≤ 0.05.

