#### Adverse event reporting and harms {22}

Any adverse events reported by the participants will be recorded in the CRF, including the time, symptoms, signs, degree, duration, laboratory test index, treatment and outcome, follow-up, and follow-up time. Common treatment-related adverse events to be tested will include subcutaneous hematoma, continuous post-needling pain, itching at the sites of the needle insertion, and dizziness.

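### Safety is a co-objective, but its only stated inference is Fisher's exact tests at 14 per arm, which cannot support a safety conclusion; exact intervals on event rates should be the main safety result.

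*Protocol article*

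**What the plan says.** Objectives {7} gives safety equal standing with efficacy: the study is to "evaluate the efficacy and safety of EA for the prevention of negative moods after SD".

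The safety analysis is one sentence under Statistical methods for primary and secondary outcomes {20a}: "Adverse events will be summarized for each group and compared using Fisher"'s exact tests. The same section sets the general threshold: "Statistical significance will be set at *p* ≤ 0.05". The sentence does not fix whether the tests are three-arm or pairwise, or whether they are run per event type or on any event.

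Adverse event reporting and harms {22} names the events: "Common treatment-related adverse events to be tested will include subcutaneous hematoma, continuous post-needling pain, itching at the sites of the needle insertion, and dizziness". It also requires the time, degree, duration, treatment and outcome of each event to be recorded.

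On exposure, the section Blank control group states: "Participants in the blank control group will not be given any treatment". The acupoint (AE) and non-acupoint (NAE) arms both receive inserted needles and current in 7 daily sessions. The 30-h deprivation is described without exempting any arm.

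Sample size {14} rests on the POMS: "the sample size will be increased to 42 participants, of which at least 14 participants will be required in each group". No power or precision is stated for adverse events. The footnote to Table 2 adds laboratory tests and an electrocardiogram as safety assessments.

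**The concern.** A between-group significance test is a poor match to the safety question here. For the three needle-site events the blank arm must have a count of zero, so needled against un-needled shows whether needling does something that nobody doubts. AE against NAE compares two sets of needle sites and is silent on the risk that the two arms share. What a reader needs is how often electroacupuncture produces a reaction and how high that rate could be. A p-value answers neither.

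At stake is the safety half of the objective. With arms this small, non-significance is the likely result even if a fifth or a quarter of needled participants react, and a result of that kind is uninformative.

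**Working it through.** **Inputs from the article.** 14 per arm; p ≤ 0.05 (taken as two-sided; the article does not say); no needling in the blank arm; needling in AE and NAE. **Assumed, because the article gives no rate:** needling harm of 20-25%, with no background events unless stated.

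**Step 1. Where 14 per arm comes from.** The article does not name the procedure that gave 33. One route that reproduces it is a normal-approximation comparison of two means, AE against blank:

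- Difference: 15.24 − 8.26 = 6.98.
- Root-mean-square SD: √[(3.18² + 5.96² + 5.42²)/3] = √25.0 = 5.00.
- n = 2(1.960 + 1.282)² × 25.0/6.98² = 10.8, so 11 per arm and 33 in total.
- Allowing for loss: 33/(1 − 0.20) = 41.25, so 42, or 14 per arm.

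Adverse events enter nowhere.

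**Step 2. What the test needs to reach p ≤ 0.05.** For a three-arm table with a, b and c participants with an event and t = a + b + c, the exact probability given t is C(14,a)·C(14,b)·C(14,c)/C(42,t). The p-value sums this over all tables with the same t that are no more probable than the one observed.

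| AE, NAE, blank (each of 14) | three-arm p |
|---|---|
| 3, 3, 0 | 0.214 |
| 4, 4, 0 | 0.094 |
| 5, 5, 0 | 0.028 |
| 3, 0, 0 | 0.095 |
| 4, 0, 0 | 0.027 |

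For AE against blank alone, 4/14 against 0/14 gives p = 0.098 and 5/14 against 0/14 gives p = 0.041.

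**Step 3. Power.** Sum the binomial probabilities of all outcomes with p ≤ 0.05. For AE against blank with a zero blank rate this is P(X ≥ 5), X ~ Bin(14, h), which is 0.130 at h = 0.20 and 0.258 at h = 0.25.

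| Test at 14 per arm | harm 20% | harm 25% |
|---|---|---|
| Three-arm, AE and NAE both affected | 14% | 27% |
| Three-arm, only AE affected | 30% | 48% |
| AE against blank | 13% | 26% |
| AE and NAE combined (28) against blank (14) | 18% | 40% |

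With both needled arms affected, three-arm power is 45% at 30% harm and reaches 81% only at 40%. With 11 completers per arm it is 10% and 19% at 20% and 25% harm.

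**Step 4. What an interval says.** For zero events in n, the exact (Clopper-Pearson) 95% upper limit is 1 − 0.025^(1/n):

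- n = 14: 23.2%.
- n = 28: 12.3%.

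For x events the limits are the 0.025 quantile of Beta(x, n − x + 1) and the 0.975 quantile of Beta(x + 1, n − x). The 4, 4, 0 result, non-significant at p = 0.094, then reads 4/14 = 29% (8.4% to 58.1%) in each needled arm and 8/28 = 29% (13.2% to 48.7%) combined. The interval makes plain a harm that the three-arm p-value would hide.

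**The case against.** The other side has a good case on several points.

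- **Form of the test.** The article says tests, in the plural, and fixes neither arms nor event unit, so a single three-arm test is only one reading. This stands. The low power does not depend on that reading: the pairwise and combined forms in Step 3 also stay below one half at 20-25% harm.
- **No decision rule.** A reader might infer that the plan will call electroacupuncture safe if p > 0.05. Nothing in the article says so; the threshold is a general one.
- **Other safety information.** Per-group summaries come first in the same sentence, event details are recorded, and laboratory tests and an electrocardiogram are collected. Fisher's test is the only stated inference, not the only safety evidence.
- **The blank arm's zero.** A reader might blame it for the low power. That would be wrong: needled against un-needled is the contrast that identifies needling harm, and a zero background does not in general reduce power. The arm size does.
- **Dilution by deprivation events.** A reader might expect shared events such as dizziness to swamp a needling signal. That requires all events to be pooled, which the article does not state, so no dilution figure is relied on here.
- **Scope.** Intervals and period-specific tables are often left to an analysis plan, and an article is condensed. But this article does choose a method for the safety comparison, and the point concerns that choice.

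**Conclusion.** The point holds in limited form. Fisher's exact tests at 14 per arm cannot carry the safety objective: at 20-25% needling harm their power runs from 13% (AE against blank, 20% harm) to 48% (three-arm, harm in AE only, 25%), so such harm would be missed more often than not under every form in Step 3. A non-significant result could not support a safety conclusion.

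The size rests on the assumed harm rates, two-sided testing, no background events and full arms of 14. The 23.2% and 12.3% upper limits depend on none of the assumed rates. The primary outcome is unaffected.

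**What to change.** In Statistical methods {20a}:

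1. Make per-arm adverse-event rates with exact (Clopper-Pearson) 95% intervals the main safety result, for AE and NAE separately.
2. For needle-site reactions, add the two needled arms combined (n = 28) as a supplement only, because the arms differ in needle sites, depths and intended De-Qi sensation and their risks may not be equal.
3. Tabulate the electroacupuncture week separately from the deprivation and follow-up period, using the event times already recorded under {22}.
4. Keep any Fisher test as descriptive, and state that the safety conclusion will be drawn from the intervals.

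The cost is wording and two tables from data already collected, with no extra participants or procedures. The safety statement becomes less favourable: even with no reactions in AE, the trial could say only that the rate is unlikely to exceed about 23%.

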### Interim analyses {21b}

There are no interim analyses planned.

### Methods for additional analyses (e.g., subgroup analyses) {20b}

There are no interim analyses planned.

### Methods in analysis to handle protocol non-adherence and any statistical methods to handle missing data {20c}

The intention-to-treat analysis will be used for all allocated participants in the baseline condition. Baseline characteristics will be summarized across the treatment groups. Missing values will be imputed by the last observation carried forward (LOCF) method.

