The damage to human health that is a result of early SD is difficult to detect, and the modern medical testing equipment makes it difficult to accurately diagnose it before it causes significant organic damage to the body. However, SD has a significant negative impact on mood. Given SD can cause serious harm to the human body, it is important to seek reliable countermeasures and preventative measures in cases where it cannot be avoided or where the disease has already occurred. Currently, there are no official guidelines for the treatment of SD. The usual treatment for SD is to examine one’s sleep hygiene in order to eliminate behavioral habits that adversely affect sleep. However, due to increased work pressure and the fast pace of life in modern society, this self-treatment method is difficult to implement. Therefore, chemotherapeutic options should be considered. Currently, modafinil is the only FDA-approved medication for the treatment of sleep disorders in shift work [11]. Appropriately administered medications such as caffeine, modafinil, and amphetamines, which excite the center, can have an anti-sleepy fatigue effect. Although these drugs have been shown to be effective in clinical use, they have also been associated with many adverse effects, such as sleep interference, mental disorders, and addiction. Moreover, when used as sleep aids, some of these drugs can exacerbate daytime fatigue if the dose is too high or if the half-life is too long. Sedative sleep aids can also worsen SD [12].

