### Data collection and management

#### Plans for assessment and collection of outcomes {18a}

Prior to the start of the trial, all data assessors will be uniformly trained in order to improve the quality of the data assessment. The primary outcome measure will be obtained using POMS while the secondary outcome measures will be obtained using PANAS and FaceReader. These three instruments have been widely used in trials related to the detection of mood changes [36–38]. During the 30-h TSD period, participants will be assessed every 3 h for a total of 11 assessments. During the 24-h after waking follow-up period, participants will also be assessed once.

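### LOCF is the only missing-data method for POMS; it is likely to understate dropouts' mood disturbance during sleep deprivation and overstate it at the after-waking follow-up

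*Protocol article*

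**What the plan says.** The section on non-adherence and missing data {20c} has two working sentences: "The intention-to-treat analysis will be used for all allocated participants in the baseline condition", and "Missing values will be imputed by the last observation carried forward (LOCF) method". It names no other method and no sensitivity analysis.

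The sample size section {14} says "The POMS will be the primary outcome measure observed", and the total is raised to 42 with the reason "To compensate for a 20% loss to follow-up". On timing, the outcome collection section {18a} says "During the 30-h TSD period, participants will be assessed every 3 h for a total of 11 assessments", and then "During the 24-h after waking follow-up period, participants will also be assessed once".

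The statistical methods section {20a} says "Continuous variables, including the POMS scores, PANAS scores, and FaceReader, will be compared among the three groups at all time points using ANOVA". The imputed values therefore feed the analysis at each session and are not confined to a supporting table.

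On the expected course of mood, the background {6a} says "However, SD has a significant negative impact on mood", and the Discussion repeats that direction. No section says that the worsening is steady, how large it is, or whether mood has recovered by the follow-up assessment.

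**The concern.** LOCF assumes that a missing score would have equalled the last one seen. This design gives reason to expect otherwise: a stressor builds up over 11 sessions, is removed, and mood is measured once more. A man whose last score is at 22:00 on the first day would have that score, taken 15 hours into deprivation, used as his 30-h score. A man lost after the 30-h session would have his most deprived score used as his recovery score.

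Two things are at stake. If the treatment works, the 30-h contrast is pulled towards zero. If it does not work but the arms lose different numbers, LOCF can create a difference. Unequal loss is plausible, because blank-arm participants know that they receive nothing. The objective of comparing effects at different time points is also exposed, because LOCF flattens the time profile of every dropout.

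**Working it through.** **The plan's own figure.** Sample size {14}: 33 evaluable participants and 20% loss. 33 / (1 - 0.20) = 41.25, or per arm 11 / 0.80 = 13.75, rounded up to 14, hence 42. The stated 42 is reproduced. The plan thus allows for about 14 × 0.20 = 2.8 men per arm with missing data.

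**Assumed inputs, not in the documents.** A higher POMS score means more disturbance. It rises linearly by D points from 0 to 30 h, with D from 5 to 15, and has recovered fully at follow-up. A fraction d of an arm is lost, the last observed session being equally likely to be any of sessions 1 to 10.

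**Bias within an arm.** A man last seen at session j has completed (j - 1)/10 of the rise and missed (11 - j)/10.

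- At 30 h the mean fraction missed is (1.0 + 0.9 + ... + 0.1)/10 = 0.55, so the bias is -0.55 × d × D.
- At follow-up the mean fraction wrongly carried is (0 + 0.1 + ... + 0.9)/10 = 0.45, so the bias is +0.45 × d × D.

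With d = 0.20 and D = 10 these are -1.1 and +0.9 points. If the loss comes before deprivation and a pre-deprivation score is carried, the 30-h bias is -d × D: -1.0, -2.0 and -3.0 for D = 5, 10 and 15. If it comes after the 30-h session, that session has no bias and the follow-up bias is +d × D.

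**Equal dropout, true benefit.** If the arms start equal, each contrast at 30 h is multiplied by 1 - 0.55 × 0.20 = 0.89. Taking the pilot means (8.26, 18.25, 15.24) as 30-h values, which the protocol does not say they are:

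| Contrast | True | Under LOCF |
|---|---|---|
| AE vs NAE | 9.99 | 9.99 × 0.89 = 8.89 |
| AE vs blank | 6.98 | 6.98 × 0.89 = 6.21 |

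**Unequal dropout, no true effect.** For a 20-percentage-point gap in loss:

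| D | Shift at 30 h | Shift at follow-up |
|---|---|---|
| 5 | 0.55 in favour of the arm losing more | 0.45 against it |
| 10 | 1.10 in favour | 0.90 against |
| 15 | 1.65 in favour | 1.35 against |

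**Simulation.** 14 per arm, 20,000 replicates, assumed between-subject SD 4 and residual SD 3, one-way ANOVA at 0.05:

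- Equal 20% dropout, no effect, D = 10: rejection rate about 0.05 at 30 h and at follow-up.
- Equal 20% dropout, true benefit (D = 5 in AE, 10 in both controls): the mean 30-h difference goes from -5.0 to about -4.45, and power from about 0.75 to 0.57. Some of that fall is simply lost data: the same ANOVA on 11 completers per arm (total SD √(16 + 9) = 5) has power 0.63.
- Dropout 40% in AE and 10% in each control, no effect, D = 10: AE minus blank is about -1.65 at 30 h with rejection rate 0.11, and about +1.35 at follow-up with rejection rate about 0.095.

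**The case against.** The strongest reply is that the size is unproven. The protocol gives a direction for mood but no shape, and a course that is not monotone would change the bias at single sessions, possibly its sign. The 20% covers the whole trial, including a baseline week and a treatment week, whereas the 30 hours are spent in hospital under constant supervision, so few men may leave during them. Under equal loss the bias dilutes a true effect and does not invent one. This stands, and it is why the figures above are illustrations and not forecasts. It does not rescue the method: loss before deprivation can make the 30-h bias larger, and a constant score remains at odds with the trial's premise.

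A reader might infer that LOCF favours whichever arm loses more people. The arithmetic does not support that in general. The sign reverses at follow-up, and during deprivation the bias follows d × D, not d alone. With an assumed 7:00 mean of 6 and the pilot means at 30 h, D is 2.26 in AE and 12.25 in NAE. If AE loses 40% and NAE 10%, the biases are -0.55 × 0.40 × 2.26 = -0.50 and -0.55 × 0.10 × 12.25 = -0.67. AE loses four times as many and still is not favoured.

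A reader might also infer that standard errors come out too small because imputed values are treated as real. In the simulation with equal 20% dropout, no effect and D = 10, the average estimated standard error of the 30-h group difference was 2.11 against an actual 2.12. Mixing early and late scores widens the spread, and the ANOVA sees it.

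**Conclusion.** The concern holds as a should-fix. LOCF is the only stated method, it enters the primary POMS comparison at every time point, and it conflicts with a design in which the stressor accumulates and then stops. The likely direction is less disturbance for dropouts during deprivation and more at follow-up. This needs only that mood worsens with time awake and improves afterwards; the protocol states the worsening but not its course, and the improvement is an inference.

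The size is conditional. Under a linear rise and evenly spread loss, 20% equal dropout removes 11% of a true 30-h contrast, and a 20-point gap in dropout shifts a null contrast by 0.55 to 1.65 points for D between 5 and 15. The planned 20% shows that the sponsor expects missing data; it does not show when or in which arm, so it does not establish that the primary result would be changed.

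**What to change.** In section {20c}, replace LOCF for POMS with a likelihood-based repeated-measures mixed model fitted by REML, with group, time and group × time, using every observed POMS score from all randomised participants. It is valid under missing at random. Name a parsimonious covariance structure suited to 42 participants. An unstructured matrix over 11 sessions has 11 × 12 / 2 = 66 parameters and should not be used. Take the group contrasts at each time point from this model, and amend the POMS sentence in {20a} to match.

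Add one sensitivity analysis that assigns dropouts a worse trajectory than the model predicts.

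Continued collection of scores after treatment is stopped is not part of this remedy. All treatment ends before deprivation begins, and later scores from a man who has ended his deprivation would not measure mood at 30 hours awake.

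The cost is a little more programming in SAS, which is already named, and a covariance assumption that has to be stated. The model itself needs no new data. The change should be made before the group codes are opened.

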### Plans to give access to the full protocol, participant level-data, and statistical code {31c}

Information from the full protocol will be published in a peer-reviewed journal. The relevant data obtained from this study protocol will be available upon reasonable request from the corresponding author.

### Oversight and monitoring

#### Composition of the coordinating center and trial steering committee {5d}

This is a monocenter study designed, performed, and coordinated at the First Affiliated Hospital of Changchun University of Chinese Medicine. Day-to-day support for the trial will be provided by the following:

Principle investigator: supervise the trial and take medical responsibility of the participants

Data manager: organize data collection and safeguard its quality

Study coordinator: trial registration, coordinate study visits, and document annual safety reports

Study physician: identify potential recruits, administer informed consent, and ensure follow-up according to the protocol

The study team will have biweekly meetings. There will be no trial steering committee or stakeholder and public involvement group.

#### Composition of the data monitoring committee, its role, and reporting structure {21a}

In accordance with the requirements of the standard for quality control and quality assurance of clinical research in TCM, a 4-level quality supervision system will be established. One supervisor will be appointed and a supervision committee set up to regularly monitor the data collected in clinical research, so as to ensure the authenticity and reliability of the project. The supervision team will supervise the entire process of information collection and input.

#### Adverse event reporting and harms {22}

Any adverse events reported by the participants will be recorded in the CRF, including the time, symptoms, signs, degree, duration, laboratory test index, treatment and outcome, follow-up, and follow-up time. Common treatment-related adverse events to be tested will include subcutaneous hematoma, continuous post-needling pain, itching at the sites of the needle insertion, and dizziness.

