The filiform needles to be used in this trial are single-use sterile acupuncture needles, namely Hwato Needles, made in Suzhou, China, 25–40 mm in length and 0.25 mm in diameter. Needles with a length of 13 mm and a diameter of 0.18 mm will be used as auxiliary needles without manipulation. De-Qi sensation will be achieved in the acupoints of the AE group by lifting and thrusting combined with twirling and rotating the needles. However, De-Qi sensation will not be achieved in the non-acupoints of the control group by the same needle manipulation methods. Needles will be retained in the AE group and the NAE control group for 30 min; afterwhich, the acupoint holes will be closed using clean cotton balls to avoid bleeding when withdrawing the needle. Participants in the two groups will be administered with 7 treatments over a period of 1 week, once a day.

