### Strategies to improve adherence to interventions {11c}

All acupuncture treatments and laboratory tests will be provided for free to improve adherence to the intervention protocol. All subjects will be required to sign a written informed consent before participating and will be compensated monetarily. Participant and acupuncturist signatures will be required after each acupuncture session to monitor adherence.

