### Relevant concomitant care permitted or prohibited during the trial {11d}

To ensure that participants within the three groups get adequate sleep (at least 7 h per night for a week before the first clinical trial) during the sleep baseline period, we will use sleep logs and actigraph (an automatic-scoring actigraph for measuring sleep in healthy adults) for recording. Throughout the study, participants will wear an actigraph (Micro Motionlogger SleepWatch®, Ambulatory Monitoring, Inc.; AMI) and report their bedtime, sleep onset latency, and wake time on a daily sleep diary. Alcoholic drinks, caffeinated beverages, prescription, over-the-counter medicines, and other preventive interventions will be prohibited during the trial.

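### Adverse events rest on participant report with no questioning common to the arms, so the treatment-week comparison with the blank arm is open to ascertainment bias for non-needle events

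*Protocol article*

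**What the plan says.** All references are to the protocol article.

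- **Capture.** Under Adverse event reporting and harms {22}: "Any adverse events reported by the participants will be recorded in the CRF". The same section names the events of interest: "Common treatment-related adverse events to be tested will include subcutaneous hematoma, continuous post-needling pain, itching at the sites of the needle insertion, and dizziness". The CRF entry also covers signs and a laboratory index. No common questioning of the three arms is described.
- **Contact in the needled arms.** The needle procedure, at the end of the section on the non-acupoint control group, states: "Participants in the two groups will be administered with 7 treatments over a period of 1 week, once a day". The adherence section {11c} adds: "Participant and acupuncturist signatures will be required after each acupuncture session to monitor adherence".
- **Contact in the blank arm.** "Participants in the blank control group will not be given any treatment". The text neither describes a treatment-week visit for this arm nor says that there is none.
- **Analysis and objective.** Statistical methods {20a}: "Adverse events will be summarized for each group and compared using Fisher’s exact tests". Objectives {7}: "This study is designed to evaluate the efficacy and safety of EA for the prevention of negative moods after SD".
- **What all arms share.** Throughout the study participants wear an actigraph and "report their bedtime, sleep onset latency, and wake time on a daily sleep diary" ({11d}). During sleep deprivation everyone is supervised constantly and assessed 11 times, and there is one assessment in the follow-up period. The note to Table 2 lists blood, urine, feces, kidney and liver tests and an ECG as the safety assessment; the table itself is not shown.

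**The concern.** When symptoms are recorded because a participant mentions them, the number recorded depends on how often the participant has someone to mention them to. In the treatment week, the period most relevant to the safety of the needling, that opportunity differs by arm as the text stands. Someone in a needled arm who feels dizzy sees a member of staff the same day. Someone in the blank arm with the same dizziness has no described occasion to say so until sleep deprivation begins.

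The between-group test treats the counts as if they had been collected alike. The blank arm is the only untreated reference, so an excess of minor symptoms in the needled arms could reflect the treatment or merely the contact, and the data could not separate the two. Safety is a stated objective, which makes the comparison worth protecting.

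**Working it through.** **1. Scheduled contacts after baseline.** One session a day for 7 days gives 7, which matches the stated number of treatments.

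| Period | Acupoint arm | Non-acupoint arm | Blank arm |
|---|---|---|---|
| Treatment week | 7 | 7 | 0 (inferred) |
| Sleep deprivation | 11 | 11 | 11 |
| Follow-up | 1 | 1 | 1 |
| Total | 19 | 19 | 12 |

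The whole difference, 19 − 12 = 7, lies in the treatment week and only against the blank arm. The 0 is an inference from the absence of treatment.

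**2. Which events are exposed.** Of the four named events, hematoma, post-needling pain and itching at needle sites arise from needling and cannot occur in the blank arm, so unequal reporting does not create that contrast. Dizziness can occur in any arm, as can symptoms that are not listed.

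**3. Effect on reported rates.** Reported rate = true risk × probability of being reported. The document gives no reporting probabilities. As an illustration, assume 0.9 in each needled arm and 0.4 to 0.6 in the blank arm, with the same true risk everywhere.

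- True risk 30%: 0.3 × 0.9 = 27% in the needled arms; 0.3 × 0.4 = 12% to 0.3 × 0.6 = 18% in the blank arm.
- True risk 50%: 45% against 20% to 30%.
- Spurious risk ratio at any true risk: 0.9/0.6 = 1.5 to 0.9/0.4 = 2.25.

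**4. Effect on the test.** Exact enumeration of the three-arm Fisher test at 0.05, with 14 per arm (Sample size {14}) and no true difference. Column heads give the assumed reporting probability in the blank arm.

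| True risk | Blank 0.4 | Blank 0.6 | Blank 0.9 (equal) |
|---|---|---|---|
| 10% | 1.4% | 1.2% | 1.1% |
| 20% | 4.7% | 3.2% | 2.5% |
| 30% | 10.1% | 5.5% | 3.5% |
| 50% | 23.7% | 9.6% | 3.8% |

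**5. Allowing for the periods with equal contact.** Step 4 applies the blank arm's lower reporting to every event. If half of the events fall in the deprivation and follow-up periods, where opportunity is equal (also an assumption), the blank arm's average reporting probability is (0.9 + 0.4)/2 = 0.65 to (0.9 + 0.6)/2 = 0.75. Rejection is then 3.9-4.8% at 30% true risk and 5.1-7.6% at 50%.

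**The case against.** The strongest reply is that this is a condensed article. Wording for eliciting adverse events and a visit schedule commonly sit in the full protocol, the CRF or the SOPs, and Table 2 and Figure 3 are not shown. A common schedule may exist there, and its absence from the article is not in itself a fault. That stands, and it is why the blank arm's zero contacts must be called an inference. What remains is that the article does state a method. It combines participant report, daily sessions in two arms only, and a formal test between groups, and that combination is open to bias if followed as written.

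Several stronger readings are tempting, and the documents do not support them:

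- **That adverse events count only if a participant reports them.** The text has no such restriction. Laboratory and ECG safety tests are listed, although they would not pick up dizziness.
- **That recording is confined to the sleep deprivation sessions.** The sentence on recording stands in the timeline for the whole trial and singles out no period or arm.
- **That the unmasked acupuncturist records the events.** The blinding section {17a} keeps acupuncturists out of data collection, a dedicated collector completes the CRF ({19}), and the session signatures are for adherence. Participants may still mention symptoms at a session.
- **That the safety comparison is biased as a whole, or uninterpretable in either direction.** The mechanism runs one way, towards over-counting in the needled arms, so finding no excess there would not be explained by it. Contact is equal between the needled arms, and equal across all arms in the later periods.

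It is also fair to say that the false rejection rate stays near or below 5% except for common symptoms under the harsher assumptions.

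**Conclusion.** The point holds in a limited form. The comparison with the blank arm is open to ascertainment bias for non-needle events in the treatment week, in the direction of over-counting in the needled arms. Comparisons between the two needled arms, needle-site events, laboratory and ECG findings, and events during deprivation and follow-up are unaffected.

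The size cannot be known from the document, because it rests on assumed reporting probabilities and on the inference that the blank arm is not seen in that week. Under the assumptions shown, distortion of the reported rates is the main effect. False rejection is material for common symptoms, small at 30% true risk, and negligible at 10%. This touches a stated safety objective and not the primary outcome. It should be changed because the remedy is cheap, and not because the trial's main conclusion depends on it.

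**What to change.** In Adverse event reporting and harms {22}, state that all three arms are asked the same fixed adverse event question on the same days. Add the question to the daily sleep diary described under {11d}, which every participant already keeps throughout the study, and repeat it at the sleep deprivation sessions and at follow-up. In Statistical methods {20a}, use these solicited reports for the between-group comparison, and list events volunteered at acupuncture sessions separately. If the full protocol already contains such a schedule, a sentence in the article saying so would be enough.

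The cost is one diary line and one CRF field. The small downside is that more minor events will be recorded in every arm.
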